### **5.3.6 Premature Discontinuation of the Trial**

The trial may be stopped by the Investigator in the event of any of the following:

1. Medical or ethical reasons that hinder the continuation of the study.
2. Poor enrollment of subjects
3. Occurrence of unexpected adverse events that are unacceptable in nature, severity and/or duration, or the frequency of known unacceptable adverse events is higher than expected.

The whole trial may be temporarily suspended or permanently terminated. If premature discontinuation of the trial is decided, the ethics committee will be informed in accordance with applicable regulations.

## **6. Study Medicine**

### **6.1 Medication**

Bisoprolol should be taken in morning orally.

Atenolol should be taken in morning orally.

### **6.2 Dosage**

Initial period (2 weeks) : Bisoprolol 5mg qd or Atenolol 50mg qd

First dosage adjustment period (2 weeks) : Bisoprolol 7.5mg qd or Atenolol 75mg qd

Second dosage adjustment period (2 weeks) : Bisoprolol 7.5mg qd or Atenolol 75mg qd

Extended treatment period (2 weeks): When patient's heart rate is lower than 65 bpm, keep the dosage for 2 more weeks.

### **6.3 Concomitant Medications and Therapies**

During the trial, any concomitant drugs, such as anti-diabetic drugs, lipid lowering drugs, anticoagulants and heart failure treatments like diuretics and ACEI, may be continued provided that these drugs do not affect heart rate. All medications used 3 months before enrollment and during the entire trial should be recorded. The dosage of these drugs may be adjusted as long as there is no effect on the heart rate.

### **6.3 Non-permitted Medicines**

CCB, ACEI, ARB, diuretics and  $\beta$ -blockers other than Concor® are not permitted during the trial.

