### 5.3.2 Inclusion Criteria :

- 25~65 years old
- Untreated mild to moderate EH
- Sinus rhythm
- RHR > 70bpm
- Can give written informed consent

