### **5.3.3 Exclusion Criteria:**

- Atrial Fibrillation (AF)/ Sick Sinus Syndrome (SSS)/ atrioventricular block 2-3 grade(AVBII -III ) without pacemaker
- Bradycardia
- hypotensive
- Unstable Angina Pectoris (UAP)/AMI/ HF (NYHA class III - IV)
- Uncontrolled diabetes mellitus (DM)
- Bronchial asthma
- Gastro-intestinal ulcer or skin ulcer
- Liver dysfunction/ renal impairment
- Treated with CCB (Calcium antagonists) ( except amlodipine) or other beta blocker.
- Glaucoma
- Known allergic/ intolerance to beta blocker
- Pregnant or lactating women
- Participation in another clinical study within the last 3 months
- Legal incapacity or limited legal capacity

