### **8.3 Endpoints**

#### **8.3.1 Primary Endpoint(s)**

The primary endpoint is BRS and central blood pressure at Last visit.

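### The two sections numbered 6.3 conflict on ACE inhibitors and diuretics, and the permissive one guards only heart rate although central blood pressure is a primary endpoint

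*Protocol*

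**What the plan says.** Two consecutive protocol sections carry the number 6.3.

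- **Concomitant Medications and Therapies** covers any concomitant drug and gives examples. Among them, "heart failure treatments like diuretics and ACEI, may be continued provided that these drugs do not affect heart rate". It adds: "The dosage of these drugs may be adjusted as long as there is no effect on the heart rate".
- **Non-permitted Medicines** names "CCB, ACEI, ARB, diuretics and" beta-blockers other than Concor, and states that they "are not permitted during the trial". It makes no exception for heart failure or any other indication.

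Three other places bear on the point.

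- Section 5.3.2 admits patients with "Untreated mild to moderate EH".
- Section 5.3.3 excludes "Unstable Angina Pectoris (UAP)/AMI/ HF (NYHA class III - IV)" and, separately, "Treated with CCB (Calcium antagonists) ( except amlodipine) or other beta blocker".
- Section 8.3.1 states: "The primary endpoint is BRS and central blood pressure at Last visit". Section 8.3.2 lists peripheral and central blood pressure among the secondary endpoints.

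**The concern.** Two drug classes are allowed by name in one section and banned by name in the next. Neither section refers to the other and no order of precedence is given. These are instructions to the people treating the patients, so the conflict cannot be left to a statistical analysis plan.

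The permissive section's only condition is that heart rate is unaffected. That protects the titration target but not the blood pressure endpoints. ACE inhibitors and diuretics lower blood pressure, and a dose change that leaves heart rate alone would satisfy the condition. Such a change could fall between the central pressure measurements at Visit 1 and at the Last visit, within the one to two months of observation given in the synopsis.

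**Working it through.** The protocol states no figure on this point, so the check is a comparison of texts.

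**Step 1: do the two rules cover the same drugs?**

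| Class | Concomitant Medications and Therapies | Non-permitted Medicines |
|---|---|---|
| ACE inhibitors | may continue, dose may change, if heart rate unaffected | banned |
| Diuretics | may continue, dose may change, if heart rate unaffected | banned |
| CCB, ARB | not named | banned |

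The direct conflict is confined to ACE inhibitors and diuretics.

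**Step 2: does eligibility remove the conflict?** Not fully. The untreated requirement in section 5.3.2 describes the hypertension and points towards the ban. But section 5.3.3 excludes only NYHA class III–IV heart failure, so a patient in class I–II is not excluded on that ground. Its prior-treatment exclusion names CCB and beta-blockers, not ACE inhibitors, ARB or diuretics. The permissive section itself expects heart failure drugs. What remains is essentially a patient with NYHA I–II heart failure who takes one of these drugs for that reason and is still judged untreated for hypertension.

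**Step 3: does the guard match the endpoints?** The guard is heart rate. Central blood pressure is a primary endpoint at the Last visit, and peripheral and central pressure are secondary. Blood pressure does not appear in the condition.

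**Step 4: can the effect be sized?** If k patients in an arm of n had changes averaging d mmHg from such adjustments, that arm's mean pressure would move by k × d / n. With 110 patients at 1:1, n = 110 / 2 = 55. (Section 5.1 also prints 96 beside each arm, which does not fit a total of 110.) The protocol gives neither k nor d, so no value follows. The between-arm difference would shift systematically only if k × d / n differed by arm. Otherwise the changes add variability.

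**The case against.** The strongest reply is that the conflict reaches almost nobody. A hypertensive patient already taking an ACE inhibitor or diuretic is hard to call untreated, which leaves the narrow group in step 2. This stands, and it limits the weight of the point.

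A second reply is that the sections can be reconciled: the first as a heart failure exception, the second as a bar on additional antihypertensives. That may have been intended, but the prohibition states no exception and neither section cites the other. An intended exception has to be written.

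A third reply is that the heart rate condition hardly matters once the prohibition governs, because the main pressure-lowering classes are then already banned. This is largely right, so the condition is not counted as a separate defect. It still applies to any unlisted drug that changes blood pressure but not heart rate.

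A reader might also infer that the per-protocol set is compromised because site investigators would judge deviations under opposite rules. The protocol does not support this. Section 8.4.1 says that deviations are settled by a medical check without saying by whom, the per-protocol set is secondary, and the ITT population serves all efficacy evaluations.

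**Conclusion.** The conflict is certain on the face of the text and should be corrected. Its practical size is small. Few patients are likely to be affected, given the untreated requirement, although the protocol states no number. This assumes that eligibility is applied as written. The expected effect is mainly noise in the blood pressure endpoints.

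A reader might infer that the central blood pressure comparison is biased. The document does not support that: it gives no frequency of use, no size of effect and no indication that adjustments would differ between arms.

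A reader might also take the prohibition as banning atenolol, since only Concor is spared. Section 5.1 makes atenolol the allocated comparator, so this is a drafting slip. The amlodipine exception in section 5.3.3, which does not match the CCB ban, is likewise a matter of alignment.

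**What to change.** Use one rule for both arms, with the prohibition governing, as this fits the untreated requirement best.

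1. In section 6.3, Concomitant Medications and Therapies, delete the heart failure example naming diuretics and ACE inhibitors, and state that the section covers only drugs not listed under Non-permitted Medicines.
2. In section 5.3.3, add an exclusion for patients who need an ACE inhibitor, ARB, diuretic or CCB, and remove the amlodipine exception. Without this, such a patient could be enrolled and then have a needed drug stopped. Clinicians should confirm the wording.
3. Extend the condition for continuing or adjusting the remaining drugs from heart rate to heart rate and blood pressure. Adding BRS is not advised, because asking investigators to judge the effect of every concomitant drug on BRS is impractical.
4. In section 6.3, Non-permitted Medicines, exempt the allocated study drug rather than Concor alone.

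The cost is protocol wording. Concomitant therapies are already recorded at the visits under section 7.1, so no data collection is added. The downside is that a few patients may become ineligible; the protocol does not allow the number to be estimated.

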### **6.4 Specification, Packaging and special precautions**

Product: Bisoprolol

Specification: 5mg

Packaging: plastic packaging, 10 tablets/ box

Producer: Merck Serono, Darmstadt, Germany

Note: stored at below 30°C. Keep out of reach of children. Expired drug should not be used

Product: Atenolol

Specification: 25mg/ 50mg

Packaging: plastic packaging, 100tablets/ box

Producer: Beijing Double-Crane Pharmaceutical Co., Ltd, Beijing, China

Note: stored at below 25°C. Keep out of reach of children. Expired drug should not be used

## **6.5 Treatment of Overdose**

The common drug overdose reactions of  $\beta$ -adrenergic receptor blockers include bradycardia, hypotension, bronchial asthma, acute heart failure and low blood sugar. There are only a small number of oral drug overdose reports on Concor® (maximal dose of 2000mg), in which bradycardia and/or low blood pressure occurs and all patients recovered after withdrawn of the drug.

If an overdose occurs, the patient should be hospitalized for observation and proper supportive treatment should be administrated.

Any overdose must be recorded in the CRF and reported to the Sponsor and relevant authorities.

## **7.1 Trial procedures and assessments**

### **7.1 Trial schedule and assessment contents**

The trial procedure and assessment contents are as follows:

1. Visit 1 -Week -1 (1 +3 day): this visit entails the following:

Before any procedures that are related to the trial is undertaken, informed consent of the patient should be obtained. Thereafter, basic information of the patient will be obtained and patients are screened for eligibility based on the inclusion and exclusion criteria.

- ①. Record birth date, gender, height, weight, waist circumstance, current medical condition and past medical history, including concomitant therapies.
- ②. Perform physical examinations, including vital signs (blood pressure, heart rate).
- ③. Blood tests: full blood count (white blood cells, neutrophils, red blood cells, hemoglobin and platelets), liver function (ALT, AST), renal function (Bun, Cr), fasting blood glucose and blood lipids (TC, TG, LDL-C and HDL-C).
- ④. 12-Lead ECG and echocardiography

- ⑤. Sepical tests: central blood pressure, BRS, BPV, HRV, Holter and 24 h-ABPM
2. Visit 2-Week 2 (14+3 days): this visit entails the following:
- ①. Perform physical examinations, including vital signs (blood pressure, heart rate), 12-Lead ECG.
  - ②. If the RHR is lower than 65 bpm, test BRS, BPV, HRV. Remain the treatment for an extended 2-week, then go for Last visit.
  - ③. Record AE and concomitant therapies.
3. Visit 3-Week 4 (28 +3 days): this visit entails the following:
- ①. Perform physical examinations, including vital signs (blood pressure, heart rate), 12-Lead ECG.
  - ②. If the RHR is lower than 65 bpm, test BRS, BPV, HRV. Remain the treatment for an extended 2-week, then go for Last visit.
  - ③. If the RHR is still higher than 65 bpm, adjust the dosage of bisoprolol or atenol according to blood pressure and heart rate. After 2 weeks, go for Visit 4.
  - ④. Record AE and concomitant therapies.
4. Visit 4-Week 6 (42+3 days): this visit entails the following:
- ①. Perform physical examinations, including vital signs (blood pressure, heart rate), 12-Lead ECG.
  - ②. If the RHR is lower than 65 bpm, test BRS, BPV, HRV. Remain the treatment for an extended 2-week, then go for Last visit.
  - ③. If the RHR is still higher than 65 bpm, directly go for Last visit.
  - ④. Record AE and concomitant therapies.
5. Last Visit- End of extended treatment:
- ①. Perform physical examinations, including vital signs (blood pressure, heart rate), 12-Lead ECG.
  - ②. Blood tests: full blood count (white blood cells, neutrophils, red blood cells, hemoglobin and platelets), liver function (ALT, AST), renal function (Bun, Cr), fasting blood glucose and blood lipids (TC, TG, LDL-C and HDL-C).
  - ③. Sepical tests: central blood pressure, BRS, BPV, HRV, Holter and 24 h-ABPM

- ④. Record AE and concomitant therapies.

## **7.2 Demographic and Other Baseline Characteristics**

### **7.2.1 Demographic Statistics**

Major demographic information is as follows:

1. Name initials
2. Birth date
3. Gender
4. Race

### **7.2.2 Informed Consent**

Participants must sign a written informed consent.

### **7.2.3 Medical history**

The following information will be collected for the medical history of the subjects:

1. To confirm whether the subjects meet the inclusion or exclusion criteria
2. Past and current medical history, smoker should be recorded smoking history.
3. Past therapies and current concomitant drugs.

### **7.2.4 Vital signs and physical examination**

Vital signs and physical examination should at least include the following items:

1. General status:
  - ✓ Heart rate (resting heart rate) measurement: sit rest for 5 minutes, no smoking, no excitatory food and beverage such as tea and coffee for 30 minutes, measurements are taken at sitting position for a continuous record of 3 minutes. Heartbeats in each minute are calculated and averaged to obtain the resting heart rate.
  - ✓ Blood pressure measurement: sit rest for 5 minutes, no smoking, no excitatory food and beverage such as tea and coffee for 30 minutes, measurements are taken at sitting position, with the elbow at the same level with the heart. Diastolic blood pressure is recorded at the fifth Korotkoff sound, repeated after 2 minutes and averaged. If the difference in diastolic blood pressure readings is > 5mmHg, measurement is repeated again after 2 minutes, and the 3 readings are averaged.
2. Physical examination of the respiratory system

3. Physical examination of the cardiovascular system
4. Physical examination of other systems
5. Body mass index:  $\text{body weight (Kg)}/\text{Height}^2(\text{m}^2)$
6. Measurement of waist circumference: At screening visit, under fasting, standing, calm breathing conditions, feet apart 25-30cm, waist circumference is measured at horizontal position at the midpoint of iliac spine and the 12th rib, with measuring tape close to but not press the skin, accurate to 0.1cm.

#### **7.2.5 Lab test items**

1. Full blood count: red blood cell count, neutrophils, hemoglobin, white blood cell count and platelet count
2. Urine test
3. Liver function (ALT, AST, ALP)
4. kidney function (BUN, Cr)
5. Chemistry tests: Na, K, Cl
6. fasting blood glucose
7. HbA 1c
8. Blood lipid levels (TC, TG, HDL-C, LDL-C)
9. 12-Lead ECG
10. echocardiography: to measure ejection fraction (EF%), fractional shortening (Fs), left ventricular end systolic diameter (LVESD), interventricular septum thickness (IVST), left ventricular posterior wall thickness (PWT)

#### **7.2.6 Special Tests**

11. Central blood pressure

Central blood pressure was performed by pressure tonometry using the integral software (SphygmoCor; AtCor Medical, Sydney, Australia) at the radial pulse, considering that this system has shown good repeatability of measurements. AIx, a measure of systemic arterial stiffness, was calculated as the difference between the second and first systolic peaks, expressed as a percentage of the pulse pressure. Because AIx depends on heart rate (HR), it was corrected for a HR of 75 bpm (AIxatHR75)

12. BRS, BPV and HRV

Measurements of SNA were performed after a 30-min rest in the sitting position. Patients were monitored noninvasively with a Finometer (Finapres Medical Systems, Amsterdam, The Netherlands; factory number: FMI. MU 00694, 00637; operation parameters: input: 220–240 V, 50–60 Hz, 100 VA) in both the supine (henceforth referred to as ‘lying’) and the standing positions. BRS was defined by the slope of the linear regression curve obtained by plotting the changes of SBP against the pulse interval. The mean value of the various slopes was calculated and used as the definitive BRS value for each subject [5,30-33]. HRV was calculated from the time-sequential analysis and was expressed as 3 components: low frequency (LF), high frequency (HF), and LF/HF ratio.

### 13. 24-hour ABPM

Blood pressure variability (BPV) was also calculated in ABPM

### 14. 24-hour Holter

For detect cardiac arrhythmia.

## 7.3 Assessment of Efficacy

Assessment of efficacy mainly includes the following items:

1. Heart rate
2. Blood pressure, including peripheral or central blood pressure.
3. BRS
4. BPV
5. HRV

## 7.4 Assessment of Safety

### 7.4.1 Management and reporting of adverse events

#### 7.4.1.1 Definitions

##### *Adverse Event*

An adverse event (AE) is any untoward medical occurrence in a subject or clinical investigation subject administered a pharmaceutical product, which does not necessarily have a causal relationship with this treatment.

An AE can therefore be any unfavorable and unintended sign (including an abnormal laboratory finding), symptom, or disease temporally associated with the use of a medicinal product, whether or not considered related to the medicinal product.

Investigators must assess the severity/intensity of adverse events according to the Qualitative Toxicity Scale as follows:

**Mild:** The subject is aware of the event or symptom, but the event or symptom is easily tolerated.

**Moderate:** The subject experiences sufficient discomfort to interfere with or reduce his or her usual level of activity.

**Severe:** Significant impairment of functioning: the subject is unable to carry out usual activities.

Investigators must also systematically assess the causal relationship of AEs to Concor® using the following definitions. Decisive factors for the assessment of causal relationship of an AE to the treatments include, but may not be limited to, temporal relationship between the AE and the treatments; known side effects of treatments; concomitant medication, course of the underlying disease or impact of other treatment.

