**To compare the safety and compliance of bisoprolol and atenolol treatment after RHR<65bpm**

### **4.1 Primary objective**

To compare the efficacy in SNS activity and central blood pressure(CAP) of bisoprolol and atenolol in essential hypertensive patients with RHR>70bpm

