#### **7.4.1.2 Recording Adverse Events**

All adverse events occurring during the study, whether serious or not, must be recorded in the Case Report Form (CRF), including its description, severity, duration (onset and resolution dates), causal relationship (i.e., whether the adverse event is related to the study treatment), any other potential causal factors, actions taken with the study drug (dose reduction, withdrawal...), required treatment, and outcome. In addition, for all serious adverse events, seriousness criteria must be documented and a specific safety report form must be completed.

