#### **7.4.1.3 Expedited Reporting of Serious Adverse Events**

As soon as the Investigator detects a serious adverse event, as defined above, associated with the study medication, he/she will report it within 24 hours (by e-mail, phone, or fax) to principal investigator [name].

The Investigator must promptly respond to any request for follow-up information or questions from the Sponsor. Serious adverse events occurring during the study must be monitored and followed up by the Investigator until stabilization or until the outcome is known, unless the subject is lost to follow-up. The Investigator will ensure any necessary additional therapeutic measures and follow-up procedures.

Reporting procedures and timelines for any new information on a previously reported serious adverse event (follow-up) are the same as for the original report.

Further to reporting serious adverse events to the Sponsor, the Investigator will comply with any applicable local pharmacovigilance requirements to report adverse reactions/events to national pharmacovigilance systems.

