#### **8.3.2 Secondary Endpoint(s)**

The secondary endpoints in this study include

- ①. Effective endpoints:
  - i. RHR
  - ii. BPV
  - iii. Blood pressure: peripheral and central blood pressure
- ②. Safety endpoints: AEs recorded in this study
- ③. Compliance Analysis

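### Section 7.4.1.1 has investigators judge adverse-event causality against Concor, one arm's product, in conflict with the wording for both arms used elsewhere in Section 7.4.1

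*Protocol*

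**What the plan says.** The safety objective covers both drugs: "To compare the safety and compliance of bisoprolol and atenolol treatment after RHR<65bpm" (Section 4, and the fourth secondary objective in the Synopsis). Four places then bear on causality or use adverse events:

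- Section 7.4.1.1, Adverse Event: "Investigators must also systematically assess the causal relationship of AEs to Concor". Atenolol is not named.
- The next sentence of that paragraph: "Decisive factors for the assessment of causal relationship of an AE to the treatments include, but may not be limited to" a list that includes timing, known side effects, concomitant medication and the underlying disease. Here the reference is plural and not tied to Concor.
- Section 7.4.1.2: every adverse event in the study goes into the CRF with its causal relationship, explained as "whether the adverse event is related to the study treatment".
- Section 7.4.1.3: the 24-hour report applies to a serious event "associated with the study medication".

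The endpoint in Section 8.3.2 is "Safety endpoints: AEs recorded in this study", with no filter on relatedness.

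**The concern.** Causality is a judgement the investigator makes when the event is recorded. If the question put to the investigator differs by arm, the answers are not comparable, and an analysis plan written later cannot restore a judgement made against the wrong drug. For a bisoprolol patient the Concor question is the right one. For an atenolol patient it asks about a drug that was not taken, and the natural answer is that the event is unrelated.

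Two things are at stake. The first is any table of drug-related adverse events, which would tend to show fewer related events on atenolol and so count against bisoprolol. The second is expedited reporting, because the trigger in Section 7.4.1.3 depends on a judgement that the event is associated with study medication.

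**Working it through.** The protocol gives no figure to reproduce on this point, so the check is a comparison of texts.

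**Step 1: what Concor is.** The protocol never says outright that Concor is bisoprolol. Section 5.3.5 makes intolerance to Concor a withdrawal criterion, Section 6.3 (Non-permitted Medicines) treats Concor as the one permitted β-blocker, and Section 6.5 describes overdose with reference to Concor. With two study drugs and bisoprolol as the product under study, the inference that Concor is the bisoprolol product is strong, but it is an inference.

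**Step 2: the question each wording asks, by arm.**

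| Place | Causality reference | Bisoprolol patient | Atenolol patient |
|---|---|---|---|
| 7.4.1.1, instruction | Concor | bisoprolol | a drug not taken |
| 7.4.1.1, next sentence | the treatments | bisoprolol | atenolol |
| 7.4.1.2, CRF item | the study treatment | bisoprolol | atenolol |
| 7.4.1.3, expedited report | the study medication | bisoprolol | atenolol |

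In the bisoprolol arm all four wordings agree. In the atenolol arm the first disagrees with the other three. At 1:1 allocation that arm is half the trial: 110 / 2 = 55 patients on the planned total. (Section 5.1 prints 96 beside each arm. Nothing here depends on which number is right.)

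**Step 3: whether the protocol says which wording prevails.** It does not. Section 7.4.1.1 is where the method of assessment is set, and its instruction is mandatory. Section 7.4.1.2 lists what is to be recorded. A site could read the study treatment in 7.4.1.2 as meaning the assigned drug, or as the Concor just named in 7.4.1.1. The instruction also announces definitions of causality, but in the text at hand only the list of factors follows, so no common scale is visible there to settle the reading.

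**Step 4: whether it is an isolated slip.** It is not. The withdrawal criterion in Section 5.3.5 names intolerance to Concor and not to atenolol. The ban on β-blockers other than Concor in Section 6.3 would, read literally, cover the comparator. The repeated one-product wording makes a literal reading of 7.4.1.1 more plausible at the site.

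**Step 5: what depends on the judgement.**

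- *All recorded adverse events (8.3.2), in the safety set (8.4.3).* Neither uses relatedness, and the set covers anyone dosed with trial drug who has follow-up safety data. Not affected.
- *A table of drug-related events.* The protocol specifies none. If one is produced, it is exposed, and the direction is against bisoprolol.
- *Expedited reporting (7.4.1.3).* The trigger is not specific to Concor. It is exposed only if the site carries over a judgement made against Concor under 7.4.1.1.

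**The case against.** The strongest reply is that this is a drafting slip which the surrounding text already corrects. The very next sentence speaks of the treatments, Section 7.4.1.2 requires relatedness to study treatment for every event in either arm, and Section 7.4.1.3 refers to study medication. For an atenolol patient each of these means atenolol. The safety endpoint counts all events whatever their cause. The section on events that do not meet the SAE definition also requires every event leading to unplanned hospitalization to be reported as an SAE, with no causality condition.

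Much of this stands, and it rules out the stronger reading. A reader might infer that causality is assessed only against Concor, that no atenolol-arm event can ever be called drug-related, and that the safety comparison is therefore one-sided by construction. The documents do not support that. Section 7.4.1.2 provides for relatedness to be recorded in both arms, so the conflict produces ambiguity and not a fixed count of zero on atenolol.

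What the reply does not remove is the contradiction. The other passages show that the intent was probably the same in both arms, but the instruction that tells investigators what to assess still names one product, and nothing says that it yields to the others.

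**Conclusion.** Section 7.4.1.1 is wrong as written: an operative safety instruction contradicts its own next sentence and Section 7.4.1.2. Severity is moderate.

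The possible effects are a difference between arms in how relatedness is judged, biasing any tabulation of drug-related events against bisoprolol, and an atenolol-related serious event being classed as not drug-associated and so missing the 24-hour report. Both require a site to follow the Concor sentence in preference to the others. The primary endpoints, the safety set and the comparison of all adverse events do not change.

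I attach no error probability. One would need an assumed rate of drug-related events, an atenolol count fixed at zero and a test on related events. The protocol gives no such rate, its CRF rule contradicts the fixed zero, and it plans no such test. The conclusion rests on one assumption, that Concor is the bisoprolol product.

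**What to change.** In Section 7.4.1.1 replace Concor with *the assigned study drug (bisoprolol or atenolol)*, and have causality judged in the same way and on one scale in both arms. Align the CRF causality item with Section 7.4.1.2. If any atenolol-arm events have already been judged against Concor, re-assess them before database lock and check whether any serious event among them should have been expedited.

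The other Concor-only passages, in Sections 5.3.5 and 6.3 (Non-permitted Medicines), also need to be reconciled with the two-drug design. How they should read is a clinical matter for the sponsor and the investigator.

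The causality change costs one phrase in the protocol and one CRF item. The only further work is re-assessing atenolol-arm events already recorded.
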